### Other outcomes

Adverse events assessed by open-ended questionsSuicidal ideation and behavior assessed using the Columbia Suicide Severity Rating Scale [18]Assessment of blinding of trial; at visit 3, the assessment from the patient and investigator is recorded in the CRF, whether they think the patient received an active treatment or placebo, or do not know, and on what reason this is based (side effect, effect on pain, or something else) (visits 2 and 3)Assessment of patients’ expectations for the study drug (visit 1)A qualitative assessment of any difference in outcome based on the pain intensity ratings in the pain diary, the PGIC, and pain relief scores (visit 3)Blood samples will be taken for a biobank, and in a subgroup of patients treated with lacosamide we will perform genetic analyses of voltage-gated sodium channels, β-subunit 1–4, and Collapsin Response Mediated protein 2.

### Data management plan

Case report forms (CRFs) for each subject screened and enrolled in this study will be completed directly in the Research Electronic Data Capture (REDCap) database to the extent possible without the use of a paper CRF. REDCap is hosted by Aarhus University. Source documents include medical records, pain diaries, and CRFs (paper or REDCap (eCRF)). The study personnel at each site will be trained in the study procedures. All investigators will have access to the final trial data set. After the study, anonymized data will be available in a data repository and will be available upon request subject to written agreement with a department head.

### Statistics

With a minimally relevant between-phenotype group difference in total pain reduction of 1.25 NRS points, a standard deviation of 1.6 within phenotype groups [5], 80% power, and a 5% risk of type I error, the sample size estimate is 27 + 27 patients for the primary objective. With a minimally relevant treatment versus placebo difference in total pain reduction of 1.5 NRS points, 80% power, and a 5% risk of type I error, the sample size estimate is 30 + 15 patients using a treatment:placebo ratio of 2:1 for the supportive objective. With an expected dropout rate of 1/6 (data available for intention-to-treat (ITT) analysis), the recruitment stops when 54 patients in each phenotype group have been randomized to lacosamide and placebo in a 2:1 ratio. Thus, we expect to randomize 108 patients. For the explorative outcome in case there is no phenotype difference, 72 patients randomized to lacosamide and 36 patients randomized to placebo in the total population in an ITT population will give > 90% power to find a minimally relevant treatment versus placebo difference in total pain reduction of 1.25 NRS points and 85% power to find a minimally relevant treatment versus placebo difference in total pain reduction of 1.0 NRS points.

Statistical analysis of the primary outcome will be performed by *t* test and of the secondary outcomes by the Mann–Whitney *U* test. Nondichotomous tertiary outcomes will be performed by *t* test or Mann–Whitney *U* test, where applicable. Since we do not expect differences in baseline between the two phenotypes [5], a major impact of baseline pain intensity on the outcome, or a center effect, we do not plan to include these as covariates in the analyses.

For the primary outcome, the delta values from the average pain intensity in the baseline week to the last treatment week (last 7 days) will be used. Response rates and other dichotomous data are analyzed using Fisher’s exact test. For the primary (and supportive) objective, we are interested in the mechanistic aspects and in understanding whether the sensory phenotype “irritable nociceptor” is a prognostic biomarker for a sodium channel blocker in therapeutic doses. Therefore, the primary analysis for the primary objective is the PP population. Missing data will not be replaced. The PP population comprises those patients who complete at least 2 weeks on stable medication with at least 100 mg bid. Thus, if patients who fulfil the PP definition stop the treatment before the 12th week, the last seven pain scores on stable medication will be used for the primary analysis, and they will be invited for an additional visit identical to visit 3. All patients who have taken at least one study capsule will be encouraged to stay in the study, complete the diary, and come for a visit after 12 weeks.

As a secondary analysis, the ITT population will be used. The ITT analysis will also be used for the explorative outcome in the whole population if there is no phenotype difference. Given a substantial dose-dependent withdrawal rate due to adverse events, the EMA suggests a conservative responder analysis and that noncompleters are defined as nonresponders [19]. Therefore, the baseline observation carried forward (BOCF) in the ITT population (all patients randomized) will be the primary imputation method, and the last observation carried forward (LOCF) will be done as a secondary imputation method. Patients will be asked to complete the pain diaries despite their withdrawal from trial medication to minimize the need for imputation.

Significance is considered at the 5% level. If there are changes to the original statistical plan, the type of change and the date of change will be documented, and the document will be signed by the sponsor.

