## Methods/design

### Objective

The primary objective is to compare the change in average intensity of neuropathic pain from the baseline week to the last week of lacosamide treatment in patients with and without the irritable nociceptor phenotype who complete at least 2 weeks on stable medication with at least 100 mg bid; that is, in the per-protocol (PP) population (Fig. 2).

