### Randomization

Randomization to the two treatments is done after the baseline period, by the pharmacy, using a computer-generated randomization list using block sizes unknown to the investigators. The patients will be stratified into two groups: patients with and without the irritable nociceptor phenotype. Allocation concealment will be ensured, as the randomization code will not be released until after the phenotype has been established and patients are randomized consecutively. The code for randomization will be stored in the pharmacy until the study is completed. Both sites receive for each randomization code a sealed envelope with information on the treatment given. The code envelope is only unsealed/opened in emergency cases if the safety of the patient requires knowledge of the randomization code.

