## Discussion

The main aim of this study is to assess the concept of stratification based on pain phenotyping in neuropathic pain. We aim to assess whether we can reproduce results from a previous study showing a better effect of the sodium channel blocker oxarbazepine in patients with neuropathic pain and the so-called irritable nociceptor phenotype [5]. Lacosamide is a sodium channel blocker with a different profile enhancing the slow-inactivation of voltage-dependent sodium channels [8]. The strength of the study is that the primary purpose is to compare the effect in two groups of patients with different sensory pain phenotypes and thus possible different underlying pain mechanisms and blinding of persons involved in the study to the pain phenotype. There are several limitations. An unrealistically high number of patients would be required to power the study to show a difference in the drug–placebo differential between the two groups of patients, so the study will need to rely on supportive evidence. A thorough analysis of previous studies would have been advantageous to assess whether the best statistical plan should be a regression analysis including, for example, baseline pain intensity, center, and escape medication. There is a possibility of discontinuation due to lacosamide’s potential side effects and a risk of unblinding due to side effects. In addition, we do not know the strength and reproducibility of the phenotype classification as only one sensory testing will be performed, and the classification into IN and NIN can be considered an arbitrary dichotomy of continuous measurements [20].

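### The t test on change scores leaves out baseline pain and centre on untested expectations, although the primary phenotype contrast is not randomised

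*Protocol article*

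**What the plan says.** In the Statistics section, "Statistical analysis of the primary outcome will be performed by" a t test, and the variable is a change score: "the delta values from the average pain intensity in the baseline week to the last treatment week (last 7 days) will be used". Under Objective, the primary contrast concerns change to the "last week of lacosamide treatment in patients with and without the irritable nociceptor phenotype", in the per-protocol population. It therefore compares two phenotype groups within one treatment arm.

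Statistics gives two kinds of reason for leaving covariates out. The first is about balance: "Since we do not expect differences in baseline between the two phenotypes", with an earlier trial cited in support. The second is about prediction: the authors also expect neither a large influence of baseline pain on the outcome nor an effect of centre. The sentence concludes: "we do not plan to include these as covariates in the analyses".

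The Discussion lists as a limitation that previous studies were not analysed to find out "whether the best statistical plan should be a regression analysis including, for example, baseline pain intensity, center, and escape medication". Under Randomization, the only stratum named is phenotype: "The patients will be stratified into two groups: patients with and without the irritable nociceptor phenotype". Centre is not named as a stratification factor.

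**The concern.** Both reasons are expectations that the article does not test, and neither is a strong ground for omitting baseline pain.

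- **Balance.** Randomisation balances lacosamide against placebo. It does not balance irritable against non-irritable nociceptor patients, and the per-protocol set is formed after randomisation. A baseline gap between phenotypes could therefore be systematic.
- **Prediction.** Baseline is useful as a covariate when it predicts the outcome, whether or not the groups differ. Patients are selected on a baseline-week mean of 4 to 9 (Inclusion criteria), so some regression to the mean is plausible. The article rules out only a major influence; a moderate one is enough to matter.
- **Change scores.** Subtracting baseline does not remove a baseline difference when change itself depends on baseline.

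At stake are some power in the primary and supportive contrasts, and a possible shift of the primary estimate in either direction. If higher baseline pain goes with a larger fall, the phenotype with the higher baseline looks more responsive than it is.

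**Working it through.** **Inputs from the Statistics section:** primary difference 1.25 points; SD 1.6; 80% power; 5% type I error (taken as two-sided); 27+27 patients; supportive difference 1.5 points with 30+15 patients (SD taken as 1.6 again).

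**Inputs not in the article, so assumed:** baseline SD (SDb) 1.0 to 1.3; slope b of final on baseline pain 0.5 to 0.8.

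**Step 1: the plan's own figures.** The t-based calculation for 1.25/1.6 gives 26.7, so 27 per group, with power 80.4%. For 1.5/1.6 at 2:1 it gives 14.07 placebo patients, so 15 with 30 on lacosamide, and power 82.6%. Both stated sizes reproduce.

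**Step 2: residual variance after adjustment.** Change has slope b − 1 on baseline, so the residual variance is 1.6² − SDb² × (1 − b)². For SDb 1.3 and b 0.5 this is 2.56 − 1.69 × 0.25 = 2.1375, a 16.5% reduction (residual SD 1.46). Power comes from the noncentral t at the plan's group sizes.

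| SDb | b | Variance reduction | Residual SD | Primary power, 27+27 | Supportive power, 30+15 |
|---|---|---|---|---|---|
| none (unadjusted) | – | 0% | 1.60 | 80.4% | 82.6% |
| 1.0 | 0.8 | 1.6% | 1.59 | 81.0% | 83.2% |
| 1.0 | 0.5 | 9.8% | 1.52 | 84.3% | 86.2% |
| 1.3 | 0.8 | 2.6% | 1.58 | 81.5% | 83.6% |
| 1.3 | 0.65 | 8.1% | 1.53 | 83.6% | 85.6% |
| 1.3 | 0.5 | 16.5% | 1.46 | 86.9% | 88.7% |

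**Step 3: the price if the authors are right.** If baseline and centre explain nothing, spending two degrees of freedom moves primary power from 80.43% to 80.37%.

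**Step 4: carry-over of a baseline gap into the primary contrast.** If the ANCOVA model holds, shift = gap × (1 − b). An assumed 0.5-point gap gives 0.5 × 0.2 = 0.10 to 0.5 × 0.5 = 0.25 points, which is 8 to 20% of the 1.25-point target. The standard error is 1.6 × √(2/27) = 0.44. With 52 degrees of freedom and no true phenotype difference, the false-positive rate becomes 5.6% (shift 0.10) to 8.7% (shift 0.25) instead of 5%.

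**Step 5: phenotype in the pooled exploratory analysis.** At 72 v 36, power for a 1.0-point effect is 85.9%. Leaving out a stratum gap g raises the SD to √(1.6² + (g/2)²). For g = 0.5 this is 1.62, and power is 85.0%.

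**The case against.** The strongest defence is that the t test is a prespecified, transparent choice. Its reasons are stated, including the expectation that baseline has no major influence on the outcome, and the Discussion discloses the alternative. The sample size fits the planned test. The article contains no baseline–outcome correlation that would refute the authors, and at the mild end of the assumed range the gain is about one power point. All of this stands. It limits the size of the point, but it does not make an untested expectation a better basis than an adjustment that costs almost nothing.

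Four stronger readings are tempting, and the article does not support them.

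- **That the plan declines to adjust for the randomisation stratum.** The quoted sentence covers baseline pain and centre, not phenotype. Phenotype is the factor compared in the primary analysis and defines the groups in the supportive one. Only the pooled exploratory analysis could omit it. That analysis runs only if no phenotype difference is found, and the article is silent on its model.
- **That the primary estimate is biased.** In a comparison of pre-existing groups, change-score and ANCOVA estimates can differ, and which is right depends on assumptions that the data cannot settle (Lord's paradox). The shift in Step 4 is conditional on a baseline gap and on change depending on baseline as ANCOVA assumes.
- **That chance imbalance biases the drug–placebo contrasts.** These contrasts are randomised, so chance imbalance is already covered by the error rate of the t test. It costs precision only.
- **That the gain is larger still.** A baseline SD of 1.5 with slope 0.5 would give a 22% variance reduction and 89% primary power. But eligibility confines baseline means to 4 to 9, and even a uniform spread over that range has an SD of only 5/√12 = 1.44.

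**Conclusion.** The point holds for baseline pain and centre. Omitting them rests on expectations that the article itself says were not checked against earlier data, and the primary contrast is one that randomisation does not protect. The likely loss is modest: about 1 to 7 percentage points of power in the primary contrast and about 1 to 6 in the supportive one. A 0.5-point phenotype gap, if present, would move the primary estimate by up to a fifth of its target difference. These sizes rest wholly on the assumed baseline SD and slope, and no figure can be given for centre. The 27+27 and 30+15 calculations are correct for the test that was planned.

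**What to change.** Before unblinding, and through the documented-change route that the Statistics section provides:

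- Make ANCOVA of last-week mean pain (or change) on baseline-week mean pain and centre the main analysis. Use phenotype as the factor for the primary contrast, and treatment as the factor within each phenotype for the supportive contrasts.
- Keep the unadjusted t test as a sensitivity analysis.
- In the conditional pooled exploratory analysis, include phenotype alongside treatment, because it is the randomisation stratum. The gain there is minor.

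The cost is one paragraph of wording and about two degrees of freedom; baseline pain, centre and phenotype are already recorded. The adjustment deals with baseline pain and centre only. It does not correct for other differences between the phenotypes or for selection into the per-protocol set, and the report should say so.

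### The exploratory total-population comparison of lacosamide with placebo on the secondary outcomes ignores the phenotype stratum used in randomisation; stratified tests would be a small, nearly free improvement

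*Protocol article*

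**What the plan says.** The Randomization section states: "The patients will be stratified into two groups: patients with and without the irritable nociceptor phenotype". The Statistics section fixes the size of the strata: "the recruitment stops when 54 patients in each phenotype group have been randomized to lacosamide and placebo in a 2:1 ratio". That is 36 lacosamide and 18 placebo per phenotype.

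Exploratory objectives and Statistics add a conditional analysis. If the phenotypes do not differ, drug and placebo are compared on the primary and secondary outcomes in everyone, with "72 patients randomized to lacosamide and 36 patients randomized to placebo in the total population in an ITT population".

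There are two secondary outcomes: a six-category pain relief rating, and escape medication, measured both as average tablets and as the number of patients taking any. The tests named are Mann–Whitney ("of the secondary outcomes by the Mann–Whitney" *U* test) and, for dichotomous data, Fisher's exact test ("Response rates and other dichotomous data are analyzed using" that test). No stratum is mentioned for either.

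The sentence ending "we do not plan to include these as covariates in the analyses" gives reasons concerning baseline differences between the phenotypes, baseline pain and centre. It does not discuss using phenotype as a stratum in the pooled comparison.

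**The concern.** Stratified randomisation balances phenotype between the arms. If phenotype also predicts the outcome, an unstratified test counts the between-phenotype spread as noise, although that spread cannot contribute to the drug–placebo difference. The test then becomes conservative and gives up power. The protocol names its tests, so this is a stated choice and not a detail left open.

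At stake is some efficiency in an exploratory comparison of two secondary outcomes. That comparison matters if phenotype turns out not to predict response.

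**Working it through.** **Inputs from the protocol.** 36 + 18 patients per phenotype, 72 v 36 in total; "a standard deviation of 1.6 within phenotype groups"; 5% level, taken as two-sided. **Assumed, because the documents give nothing:** the phenotype shift *s* on the outcome, the category cut-points for pain relief, and the response rates.

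**Step 1: reproduce the plan's own figure.** For 72 v 36 the standard error is 1.6 × √(1/72 + 1/36) = 0.327. For a 1.0-point difference, power = Φ(1.0/0.327 − 1.96) = Φ(1.10) = 86.5% (85.9% by noncentral *t*), against the stated 85%. For 1.25 points it is 96.9% (96.7%), against the stated >90%. The plan's figures hold. They concern the pain score under a *t* test, not the secondary outcomes.

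**Step 2: mechanism.** With two equal strata shifted by *s*, the unstratified test uses variance 1.6² + *s*²/4, while the arm difference really varies with 1.6². The actual error is about 2[1 − Φ(1.96 × √(1 + *s*²/(4 × 2.56)))].

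- *s* = 0.5: factor 1.012, error 4.7%
- *s* = 1.0: factor 1.048, error 4.0%
- *s* = 1.25: factor 1.074, error 3.5%

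**Step 3: ranked six-category outcome.** Simulation, 20,000 trials per row, categories cut from a normal with SD 1.6. Power is for a 1.0-point drug effect.

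| *s* | Error, Mann–Whitney | Error, van Elteren | Power, Mann–Whitney | Power, van Elteren |
|---|---|---|---|---|
| 0 | 4.9% | 4.9% | 82.8% | 82.7% |
| 0.5 | 4.8% | 5.1% | 81.8% | 82.3% |
| 1.0 | 4.1% | 5.0% | 79.1% | 81.5% |
| 1.25 | 3.5% | 4.9% | 78.0% | 81.7% |

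**Step 4: dichotomous outcome.** Simulation, 20,000 trials per row. Error is with no drug effect; power is for a 25-point drug effect. CMH is the Cochran–Mantel–Haenszel test stratified by phenotype.

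| Control rates by phenotype | Error: Fisher / plain chi-square / CMH | Power: Fisher / CMH |
|---|---|---|
| 25%, 25% | 3.6 / 5.0 / 4.7% | 69.9 / 71.1% |
| 30%, 20% | 3.6 / 4.9 / 4.8% | 69.5 / 71.7% |
| 35%, 15% | 3.0 / 4.5 / 4.9% | 70.5 / 73.9% |
| 45%, 15% | 2.9 / 3.8 / 5.0% | 69.2 / 75.6% |

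The plain chi-square column separates the two causes. With equal rates, the whole shortfall (3.6% v 5.0%) is Fisher's discreteness. At 45% v 15%, discreteness accounts for 3.8 − 2.9 = 0.9 points and ignoring the stratum for 5.0 − 3.8 = 1.2 points.

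Simulation error is about ±0.3 points for error rates and ±0.6 for power.

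**Step 5: how often would pooling occur with a real shift?** Read the condition as a non-significant *t* test between phenotypes on lacosamide, 36 v 36. This reading is an assumption. The standard error is 1.6 × √(2/36) = 0.377.

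- *s* = 0.5: Φ(1.96 − 1.33) = 74%
- *s* = 1.25: Φ(1.96 − 3.31) = 9%

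Simulation on a continuous outcome gives the same values. Among simulated trials that met the condition, Mann–Whitney error was about 4.0–5.3% over *s* = 0 to 1.25.

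**The case against.** The strongest reply is that the harmful scenario is largely excluded by design. Pooling happens only if no phenotype difference is seen, and the Objective section expects none in the response to placebo. Without a phenotype effect Mann–Whitney loses nothing, and a shift large enough to cost 4 points would seldom allow pooling. Fisher's conservatism is mostly discreteness, and preferring an exact test is legitimate. The analysis is exploratory.

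Most of this stands, and it limits the point to an efficiency gain. Two parts do not dispose of it. A non-significant result is weak evidence of no effect: a true 0.5-point shift would pass about 74% of the time. And if the condition concerns the pain score, it does not screen paracetamol use, which the Study drugs section allows for any type of pain and which could differ by phenotype for other reasons.

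A reader might infer more than the documents support:

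- **That the tests necessarily run below 5% and lose power.** For Mann–Whitney this needs a prognostic phenotype, and the documents give no such effect.
- **That the loss is about 7 points.** That figure (69.9% v 77.3%) needs a phenotype shift of a full SD. On the pain scale this is 1.6 points, more than the 1.25 points the trial is sized to detect.
- **That the pooled 30% and 50% response rates are affected.** These are tertiary outcomes, and only primary and secondary outcomes are named for pooling. The dichotomous secondary outcome is the number of patients taking any escape medication.
- **That the main conclusions are at risk.** The primary objective compares phenotypes and the supportive one compares drug with placebo within each phenotype, so a phenotype-stratified test applies to neither.

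**Conclusion.** The point holds as a small, optional improvement. The pooled tests leave out the factor used to stratify randomisation. If that factor is prognostic for the secondary outcomes, stratified tests bring the error back to about 5%. For Mann–Whitney they recover between 0 and about 4 points of power over shifts of 0 to 1.25. For the dichotomous outcome they gain about 1 to 6 points over the rates tried, part of which comes from leaving Fisher's discreteness behind.

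The planned tests err on the conservative side, so no false-positive risk arises. The sizes rest on assumed shifts, cut-points and response rates. The direction does not, provided phenotype is prognostic.

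**What to change.** Add one sentence to the Statistics section, limited to the total-population comparison of lacosamide with placebo. It should name the van Elteren test stratified by phenotype for pain relief and number of paracetamol tablets, and the Cochran–Mantel–Haenszel test stratified by phenotype for the proportion taking any escape medication. If response rates are also to be pooled, they should get the latter test too. Keep the planned tests for comparisons between phenotypes and within a phenotype.

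The protocol already provides for documented, dated and signed changes to the statistical plan. No extra data or patients are needed. The downsides are that the Cochran–Mantel–Haenszel test is not exact (its simulated error was 4.7–5.0% here), and that the van Elteren test gives up to about 0.4 points of power if phenotype is not prognostic.

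### Optional gain in power: replace Fisher's exact test, which is valid but conservative at these group sizes, with Boschloo's test for the responder and other dichotomous outcomes

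*Protocol article*

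**What the plan says.** The Statistics section states: "Response rates and other dichotomous data are analyzed using Fisher’s exact test". The outcomes this covers include the 30% and 50% pain reductions (Tertiary outcomes) and, within one secondary outcome, the number of patients who take any escape medication. The level is given once: "Significance is considered at the 5% level".

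The same section fixes the group sizes. For lacosamide against placebo within a phenotype, "the sample size estimate is 30 + 15 patients using a treatment:placebo ratio of 2:1 for the supportive objective". After allowance for a dropout of 1/6, recruitment is 54 per phenotype at 2:1, that is 36 + 18. The section states no expected response rate, and no power for any dichotomous outcome.

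For the continuous outcomes it says "Statistical analysis of the primary outcome will be performed by *t* test and of the secondary outcomes by the Mann–Whitney *U* test". It does not say which form of the t test is meant.

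**The concern.** In a 2x2 table with few patients, Fisher's test conditions on both margins, and only a few p-values are possible. The largest attainable p-value at or below 5% is often well under 5%, so part of the allowed error goes unused. An unconditional exact test can use some of it. Boschloo's test does so with Fisher's own p-value as the ranking, so it never loses a rejection that Fisher's test would have made.

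At stake is power on the responder rates. These are the most directly readable clinical support for the pain-score result, and the Discussion accepts that the trial is too small to test the phenotype difference in drug effect directly and must lean on supporting evidence. Because Fisher's test is named in the text, this is a stated choice and not a detail left open for the analysis plan.

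**Working it through.** **Inputs from the Statistics section.** Level 5% (sidedness is not stated; two-sided is assumed and reproduces the sample sizes). Supportive comparison: 1.5 NRS points, SD 1.6, 80% power, 2:1. Dropout 1/6; 54 randomized per phenotype.

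**The plan's own sizes first.** With placebo size n and lacosamide size 2n, the normal formula is n = 1.5 × (1.6/1.5)² × (1.960 + 0.842)² = 1.5 × 1.138 × 7.85 = 13.4, so 14 + 28. Exact t-test power is 79.8% at 28 + 14 and 82.6% at the stated 30 + 15, so the stated figure is a slight round-up and is sound. Dropout: 45 / (5/6) = 54 = 36 + 18.

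**Group sizes for the binary outcomes.**
- Lacosamide against placebo within a phenotype: 36 + 18 randomized; 36 × 5/6 = 30 and 18 × 5/6 = 15 evaluable.
- Between phenotypes on lacosamide: 36 + 36 randomized, 30 + 30 evaluable.
- Whole population, if there is no phenotype difference: 72 + 36.

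**Method.** Enumerate every table (x1, x2). For a rejection region R, P(reject) = Σ over R of Bin(x1; n1, p1) × Bin(x2; n2, p2). Size is this sum at p1 = p2, maximised over a grid of common rates; power is the sum at p1 ≠ p2. Fisher's region is {two-sided Fisher p ≤ 0.05}. Boschloo's region is {two-sided Fisher p ≤ c}, with c the largest cut-off whose maximum size is at most 5%. At every size listed c exceeds 0.05 (0.063 at 30 + 15; 0.069 at 30 + 30 and 36 + 18), so Boschloo's region contains Fisher's.

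**Maximum true size.**

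| Groups | Fisher | Boschloo |
|---|---|---|
| 30 + 15 | 3.3% | 4.9% |
| 30 + 30 | 2.7% | 4.7% |
| 36 + 18 | 4.2% | 4.9% |
| 36 + 36 | 2.8% | 4.9% |

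**Power, Fisher / Boschloo, in %.** The rates are assumptions.

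| Rates | 30 + 15 | 36 + 18 | 30 + 30 | 36 + 36 |
|---|---|---|---|---|
| 50% v 15% | 58.6 / 68.9 | 70.1 / 74.9 | 77.7 / 82.1 | 86.1 / 90.8 |
| 50% v 20% | 41.8 / 53.2 | 53.9 / 57.8 | 59.6 / 67.1 | 69.6 / 77.2 |
| 40% v 10% | 52.3 / 57.6 | 60.5 / 69.7 | 70.5 / 74.3 | 80.0 / 86.4 |
| 60% v 25% | 52.5 / 62.4 | 67.9 / 68.4 | 71.9 / 79.3 | 79.7 / 85.7 |

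The gains for these pairs are about 5 to 11 points at 30 + 15, 0.5 to 9 at 36 + 18, 4 to 8 at 30 + 30 and 5 to 8 at 36 + 36. At 72 + 36 they are 0.1 to 1.6 points.

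**Sensitivity.** Over a wider grid (placebo 10% to 40%, differences of 20 to 40 points), the gain at 30 + 15 runs from 1.4 to 11.4 points (median 7), and at 36 + 18 from 0.2 to 9.3 (median about 2). One extra patient also matters: for the four pairs above, 31 + 15 gives gains of 0.8 to 7.6 points and 30 + 16 gives 1.3 to 5.9.

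**The case against.** The strongest answer is that Fisher's test is a conventional small-sample choice that keeps the error below 5%, so the plan states nothing wrong. The outcomes are mostly tertiary, no power is claimed for them, and no stated figure is falsified. All of this stands, and it is why the point is optional. A reader might infer from the sizes near 3% that the test fails its nominal level. It does not: it stays on the safe side, and the only cost is power.

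The size of the gain is also open to challenge. It rests on assumed response rates and depends on the counts. With all randomized patients, which is the relevant set when non-completers count as non-responders, the typical lacosamide-placebo gain falls to about 2 points, and in the whole population it nearly vanishes. That stands too, though in the between-phenotype contrast the gain does not shrink with all patients included.

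A second tempting reading is that the t tests in the 2:1 comparisons are also off their level. A pooled-variance test at 30 + 15 would run at about 8.5% or 2.7% if the lacosamide SD were 0.67 or 1.5 times the placebo SD, while Welch's form stays at about 5%. The documents do not support this as a finding. They do not fix the pooled form; the single SD ("a standard deviation of 1.6 within phenotype groups [5") is a sample-size input and not an analysis rule; and no unequal SDs are given. Baseline-carried-forward zeros cannot be the cause in the supportive comparison, because that is per protocol with no replacement of missing data. The primary comparison, planned at 27 + 27, stays at 5.0% to 5.1% even under the pooled form for SD ratios from 0.5 to 2.

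**Conclusion.** The point holds as an optional improvement to a stated method, not as an error. In the phenotype-level comparisons Fisher's test leaves between roughly one and two percentage points of the 5% unused even at its least conservative (maximum size 4.2% at 36 + 18, 2.7% at 30 + 30). Boschloo's test recovers part of this without exceeding 5% and without losing any Fisher rejection. The benefit is usually several points of power in the between-phenotype contrast. In the lacosamide-placebo contrast within a phenotype it ranges from under 1 to about 11 points, and for the whole population it is negligible. These figures assume a two-sided 5% level, the planned or dropout-adjusted counts, and response rates that the protocol does not supply. No validity problem follows, the primary analysis is untouched, and nothing is concluded against the t tests.

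**What to change.** In the Statistics section, replace Fisher's exact test for dichotomous outcomes, within phenotype and between phenotypes, by Boschloo's exact unconditional test at the two-sided 5% level. State that the two-sided Fisher p-value is the ordering statistic: doubling a one-sided p-value gives a different rejection region, which was not checked here. Report each comparison with a risk difference and a 95% confidence interval, and name the interval method.

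The cost is about one sentence, with no change to sample size, data collection or outcomes. The protocol already provides for dated and signed changes to the statistical plan; this one should be recorded that way before unblinding. The choice between pooled and Welch t tests can be left to the analysis plan.
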